# Effect of *Ishige okamurae* extract on musculoskeletal biomarkers in adults with relative sarcopenia: Study protocol for a randomized double-blind placebo-controlled trial

**DOI:** 10.3389/fnut.2022.1015351

**Published:** 2022-09-27

**Keywords:** dietary supplements, sarcopenia, *Ishige okamurae*, muscle, randomized clinical trial, adult, brown seaweeds, functional foods

## Abstract

**Introduction:**

Sarcopenia is a phenomenon in which skeletal muscle mass decreases with age, causing many health problems. Many studies have been conducted to improve sarcopenia nutritionally. *Ishige okamura* (IO) is a genus of brown algae and plays a role in anti-diabetes, anti-obesity, and myogenesis. However, the effect of IO extract (IOE) on human muscle strength and mass is unclear. Therefore, we will examine the impact and safety of consumption of IOE for 12 weeks on muscle strength and mass in middle-aged and old-aged adults with relatively low skeletal muscle mass.

**Materials and methods:**

A randomized controlled trial is conducted on 80 adults aged 50–80. A total of 80 participants will be enrolled in this study. Participants assign IOE-taking group (*n* = 40) and placebo taking group (*n* = 40). At a baseline and 12 weeks after treatment, the following parameters of the participants are checked: knee extension strength, handgrip strength, body composition, laboratory tests, dietary recall, physical activity, and EQ-5D-5L.

**Discussion:**

The present study will be the first randomized, double-blind placebo-controlled trial to examine the efficacy and tolerability of IOE supplementation in adults with relatively low muscle mass. The nutritional intake and physical activity that might influence muscle strength and mass will be considered as covariates for transparency of results. The results of this study will provide clinical evidence for sarcopenia patients with nutrient treatment.

**Clinical Trial Registration:**

www.clinicaltrials.gov/, Identifier: NCT04617951.

## Background

After reaching about 50% of the total body weight at a young age, the muscle mass decreases gradually after the age of 30, reaching nearly 25% by 75–80 (1). With age, reduced physical activity, decreased protein synthesis, decreased anabolic hormone concentration, and progressive loss of motoneurons lead to sarcopenia (2–4). Sarcopenia is a disorder of skeletal muscle that reduces muscle strength and size (5). Sarcopenia can rise the event of fragility, falls, hospitalization, and mortality (5–7). Therefore, sarcopenia has been recognized as a disease since its registration in the International Classification of Disease, Tenth Revision, Clinical Modification on October 1, 2016 (8, 9). In recent years, several pharmacological treatments, including synthetic drugs and hormones, have been tested for the improvement of sarcopenia in clinical trials (10–12). However, it has been reported that testosterone may increase the risk for cardiovascular adverse events. Selective androgen receptor modulators have been used to avoid the side effects of anabolic steroids, but constipation, dyspepsia, or nausea have also been observed in studies (10). Growth hormone increased lean body mass and decreased fat mass; however, adverse events such as soft tissue edema, arthralgias, and carpal tunnel syndrome were significantly increased in the clinical trial (11). Therefore, there has been growing interest in identifying functional food with few side effects to prevent sarcopenia. Functional foods that have been recently studied to be effective against sarcopenia include curcumin, resveratrol, catechin, soy protein, ginseng, and *Schisandra chinensis* Baillon extracts (12, 13). A previous study showed that sea grape (*Caulerpa racemosa*) extracts improved serum peroxisome proliferator-activated receptor γ coactivator 1α, which plays a role in promoting muscle tissue remodeling after 4 weeks in men with obesity (14).

*Ishige Okamura* (IO) is a genus of brown algae, growing attached to the rocks from Geoje Island on the southern coast to the southwest coast and all over Jeju Island, South Korea. It is also distributed and abundant throughout the coastal areas of many countries in the Northwest Pacific region (15). IO extracts (IOE) are known to have anti-obesity by inhibiting lipid accumulation and anti-diabetic effects by improving insulin resistance and protecting pancreatic β-cells dysfunction *in vitro and vivo* (16, 17). Lately, IO extract (IOE) has been reported to promote the pathway to synthesis of muscles through the myostatin/Smad3 pathway and enhance protein phosphorylation of the growth regulatory axis *in vitro* (18–20) and increase muscle mass and strength *in vivo* (21). IOE showed no significant toxicity *in vivo* or animal models (22). However, no randomized, placebo-controlled trial in humans has explored the effects and safety of IOE in adults with low muscle mass. Based on previous studies, we hypothesized that IOE improves muscle strength and function in adults. Therefore, the present study investigates whether IOE increases muscle mass and strength with regular walking compared with placebo and normal walking in middle-aged and older adults with relatively lower muscle mass.

## Materials and methods

### Study design and ethical aspects

The study is designed as a randomized, placebo-controlled, double-blind clinical trial. All subjects gave their informed consent for inclusion before participating in the study. The study will be conducted per the Declaration of Helsinki, and the Institutional Review Board Ethics Committee at Pusan National University Yangsan Hospital (IRB No. 02-2020-029) approved the protocol. Table 1 shows the data collection schedule. The flow of participants through the controlled interventional trial is depicted in a tentative CONSORT conform diagram (Figure 1).

**Table 1 T1:** Data collection schedule.

	**V1**	**V2**	**V3**	**V4**
**Participant information**				
Informed consent	**×**			
Selection (inclusion/exclusion criteria)	**×**	**×**		
Participant information	**×**			
History taking	**×**			
Physical examination	**×**	**×**	**×**	**×**
Vital sign	**×**	**×**	**×**	**×**
**Outcomes**				
Knee strength test		**×**		**×**
Hand grip strength test		**×**		**×**
Body composition analysis		**×**		**×**
Clinical laboratory test		**×**		**×**
**Questionnaires**				
Nutrition assessment		**×**		**×**
Quality of life		**×**		**×**
Waking log		**×**	**×**	**×**
**Test supplementation distribution**		**×**	**×**	
**Safety and compliance**				
Safety laboratory test	**×**			**×**
Adverse reaction			**×**	**×**
Concomitant drug taking	**×**	**×**	**×**	**×**
Compliance monitoring			**×**	**×**

V1, screening at visit 1; V2, baseline assessment at visit 2; V3, compliance and safety monitoring at visit 3; V4, end of intervention at visit 4.

**Figure 1 F1:**
[figure not shown]
Tentative CONSORT flow diagram.

### Participant recruitment and screening

Study candidates are recruited through bulletin boards and social media advertisements at a tertiary hospital in Yangsan-si, South Korea. Adults aged 50–85 are screened for eligibility according to the inclusion and exclusion criteria (Table 2). This study defined relatively low skeletal muscle mass as <110% of the standard lean mass measured using the body composition analyzer (InBody 720) (13). All subjects may withdraw their consent at any time during the study. Subjects of the following criteria will be considered to have dropped out or discontinued participation in the trial and will be excluded from the per-protocol analysis: failure to take the IOE supplementation or placebo for five consecutive days, failure to attend follow-up assessments, and poor compliance (< 80%). This study protocol is similar to our previously published study (13).

**Table 2 T2:** Eligibility criteria.

**Inclusion criteria** •Aged between 50 and 85 years • Body mass index ranging from 18.5 to 30.0 kg/m^2^ • Relatively low skeletal muscle mass (< 110% of the standard lean mass measured using the body composition analyzer InBody 720) • Capable of normal physical activity
**Exclusion criteria** • Malignant tumor or severe cardiovascular diseases such as angina or myocardial infarction within the last 6 months • Any central bone fracture within the last 1 year • Uncontrolled hypertension (Blood pressure ≥ 160/100 mmHg) • Uncontrolled diabetes (fasting glucose level ≥ 160 mg/dL) • Uncontrolled hyperthyroidism or hypothyroidism • Abnormal liver function (aspartate aminotransferase or alanine aminotransferase concentration, greater than twice the upper limit of normal) • Abnormal renal function (creatinine concentration, greater than twice the upper limit of normal) • Severe gastrointestinal symptoms such as heartburn and indigestion • Those who participated in other drug clinical trials within the past 1 month • Psychiatric illnesses such as severe depression, schizophrenia, and drug addiction • Alcohol abusers • Those who are pregnant, lactating, or planning to become pregnant during the clinical trial period • Allergic reaction to the constituent foods • Those who are judged unsuitable by the researcher for other reasons

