### Outcomes

All outcomes were measured at baseline and after 12 weeks. The primary outcome measure was the change from the baseline in the peak torque (TQ) at 60°/s of knee extension/flexion representing muscle function at 12 weeks of IOE or placebo use. The secondary outcome measures were changes in appendicular skeletal mass (ASM)/height^2^ (kg/m^2^) (appendicular skeletal mass index, ASMI), ASM/weight x 100 (skeletal muscle mass index, SMI), total body fat (%), trunk body fat (%), hand grip (kg), serum creatinine, pyruvate, lactate, and high sensitivity C-reactive protein during the 12-week treatment period.

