### Statistical analyses

Shapiro–Wilk's test will be used for the normality distribution assessment of all variables (Table 3). A *p* < 0.05 will be considered statistically significant. Data will be analyzed using IBM SPSS Statistics 22.0 (IBM Inc., Armonk, NY, USA) and R software version 3.6.2 (http://www.r-project.org/). Intention-to-treat analysis will be primary for comparisons of outcomes between the IOE and placebo groups, with multiple imputation of missing data. Five imputed data sets will be created for missing values at the 12-week follow-up for all variables. The outcome also will be compared between the two groups using a per-protocol (PP) analysis. Intergroup comparisons of baseline characteristics will be performed using the 2-sample *t*-test or Mann-Whitney's *U*-test for continuous variables and the chi-square test or Fisher's exact test for categorical variables. ANCOVA or rank ANCOVA will be used for the primary analysis, with adjustments for the variables if there is a difference between the two groups at the start of the study and there is a difference in exercise and diet during the study period, all of which will be calculated as a delta. All randomized patients exposed to at least one dose of study intervention will be included for safety analyses, as our previous study (13).

**Table 3 T3:** Study variables.

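### Non-adherence is classed as leaving the trial, so measurable week-12 outcomes may be imputed in the primary intention-to-treat analysis

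*Protocol article*

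**What the plan says.** The section on participant recruitment and screening of the protocol article lists three events: "failure to take the IOE supplementation or placebo for five consecutive days", missed follow-up assessments, and compliance under 80%. It attaches two consequences to them. The first is a status: "Subjects of the following criteria will be considered to have dropped out or discontinued participation in the trial". The second, in the same sentence, is exclusion from the per-protocol analysis.

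The section on statistical analyses then states: "Intention-to-treat analysis will be primary for comparisons of outcomes between the IOE and placebo groups, with multiple imputation of missing data". It adds: "Five imputed data sets will be created for missing values at the 12-week follow-up for all variables". Per-protocol is a further comparison: "The outcome also will be compared between the two groups using a per-protocol (PP) analysis".

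On timing, the outcomes section states: "All outcomes were measured at baseline and after 12 weeks". Table 1 agrees, with strength, body composition and laboratory outcomes at V2 and V4 only. It places compliance monitoring at V3 and V4. The study intervention section bases compliance on capsule counts at visits and has intake diaries handed in at visits.

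**The concern.** Removing non-adherers from the per-protocol set is normal. Classing them as having left the trial is a different matter. Of the three listed events, only missed follow-up makes an outcome missing by itself. A participant who skipped capsules can still come to V4 and be tested on the dynamometer.

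If the status is applied as written, non-adherence found at V3 ends participation before any post-baseline outcome exists, and the week-12 value falls to multiple imputation. ITT is meant to estimate the effect of assignment whatever the adherence. If the observed outcomes come largely from adherers, ITT and per-protocol rest on nearly the same observed data, and the primary result drifts towards the effect in people who kept taking the capsules. The missing data would also have been avoidable.

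**Working it through.** **1. The plan's own figure.** The sample size section gives 40 per group after a 20% dropout allowance. 32 / (1 − 0.20) = 40, so 40 fits 32 evaluable per group; 33 × 1.2 = 39.6, rounded up to 40, fits as well. Effect size, SD and power are left to the earlier study, so the figure cannot be reproduced further. It is not in dispute here. The 20% is a general dropout allowance, not a non-adherence rate.

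**2. How far the five-day criterion reaches.** Twelve weeks is 12 × 7 = 84 days. One five-day gap and no other missed dose leaves 79/84 = 94.0% compliance. The criterion can therefore class as out of the trial someone far above the 80% limit.

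**3. Who could lose a measurable outcome.** Table 1 gives two cases.
- Non-adherence found at V3: no post-baseline outcome exists yet. If participation ends there, the week-12 value is missing.
- Non-adherence found only at V4: outcomes are measured at that same visit, so an observed value can exist and nothing needs imputing.

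**4. Size if values are missing and imputed from adherers.** Let q be the share affected and f the share of the supplement's effect that they keep. Both are assumptions. It is also assumed that those affected do not otherwise differ in prognosis.
- True ITT effect / adherer effect = (1 − q) + q × f
- Estimate after imputation from adherers / adherer effect = 1
- Overstatement = 1 / [(1 − q) + q × f] − 1

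| q | f = 0 | f = 0.5 |
|---|---|---|
| 5% | 1/0.95 − 1 = 5.3% | 1/0.975 − 1 = 2.6% |
| 10% | 1/0.90 − 1 = 11.1% | 1/0.95 − 1 = 5.3% |
| 20% | 1/0.80 − 1 = 25% | 1/0.90 − 1 = 11.1% |

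For a participant with a single five-day gap, f is probably much higher. If the effect kept is in proportion to days taken, f = 79/84 = 0.94. Even at q = 20% the overstatement is then 1 / (0.80 + 0.20 × 0.94) − 1 = 1/0.988 − 1 = 1.2%.

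**5. Check by simulation.** Settings: 40 per arm, 3,000 runs, five imputations, ANCOVA on baseline, and normal imputation from arm and baseline fitted to those who remained. The adherer effect was set to the one detectable with 32 per arm at 80% power and two-sided 0.05: (1.960 + 0.842) × √(2/32) = 0.70 SD. Non-adherers gained nothing (f = 0).

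| q | V4 values kept | V4 values missing, imputed |
|---|---|---|
| 5% | 0.66 | 0.70 |
| 10% | 0.63 | 0.70 |
| 20% | 0.56 | 0.70 |

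This matches the formula. With imputation the estimate stays at the full-adherence effect, and with observed values it falls to the ITT effect.

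**The case against.** The strongest reply is that the article never says that non-adherers go unmeasured. The only analysis consequence it states is per-protocol exclusion. Imputation covers missing values only, and an observed V4 value is not missing. Missed follow-up is listed separately from the adherence criteria, which would be redundant if non-adherence already ended assessment. On this reading the list is a per-protocol exclusion list with loose wording. Final compliance below 80% is also established at V4, when the outcome can be measured.

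Much of this stands, and it makes the point conditional. It does not remove it. The status of having left the trial is stated alongside the per-protocol exclusion, its ordinary meaning is no further assessment, and nothing in the article says that non-adherers are still measured at V4.

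A reader might go further in three ways that the article does not support.
- That ITT will replace non-adherers with values modelled on compliers. No imputation model or reference group is given, and that detail may properly sit in an analysis plan that is not shown.
- That the five-day and 80% criteria contradict each other. They are alternatives, one for a continuous gap and one for total intake, and a participant can meet either alone.
- That the 20% allowance, 0.20 × 80 = 16 participants, measures the outcomes lost to this rule. That allowance also covers consent withdrawals and missed visits, whose values are truly missing.

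**Conclusion.** The point holds in conditional form. The article merges non-adherence with leaving the trial, and a literal application would send measurable week-12 outcomes to imputation in the primary analysis. The people exposed are those whose non-adherence is found before V4.

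Given missing-at-random imputation and the assumed shares above, the ITT estimate would be too large by 2.6% to 25%. The 25% is an extreme: it needs 20% affected and no benefit kept by any of them, which is implausible for someone who is 94% compliant. The overstatement is zero if V4 values are observed and used. Because the mechanism scales a real effect, it also creates no apparent benefit when the supplement does nothing. Unequal loss between the arms is possible, but nothing in the article indicates it.

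This is a cheap improvement that protects the meaning of the primary analysis. It is not a demonstrated bias.

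**What to change.** Separate the two ideas in the recruitment and screening section, and carry the same wording into the analysis section:
- The five-day and under-80% criteria define exclusion from the per-protocol set only.
- V4 outcomes are sought from every randomised participant who has not withdrawn consent.
- Observed week-12 values enter the ITT analysis whatever the adherence.
- Only values that could not be obtained are imputed.

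This takes a sentence or two, and V4 is already scheduled. The cost is some effort to bring non-adherers to V4 and a possibly smaller effect estimate, which is the one that ITT is meant to give. If the sponsor already measures non-adherers at V4, the change only records existing practice.

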### Randomization

The procedure of randomization has been reported elsewhere (13). Eighty participants will be finally enrolled after undergoing baseline measurements. They are randomly assigned to either one of the intervention groups with IOE (IOE) or the control group with placebo through block randomization using randomized numbers and given identification numbers on recruitment. Randomization codes were created by an expert in statistics using nQuery Advisor 7.0. Those responsible for deciding on study eligibility and conducting the measurements are unaware of the randomization results throughout the whole study process.

### Study intervention

In a previous animal study (22), efficacy started to show from a 50 mg/kg dose of IOE, and IOE significantly upregulated the grip strength in a dose-dependent manner. However, both the administration of 100 and 200 mg/kg doses of IOE similarly fully recovered lean mass. Therefore, 100 mg/kg was selected as the efficacious dose of IOE for improving muscle strength for safety and efficacy in the present study. The dose was converted to a human equivalent dose based on the person's body surface area, 480 mg for individuals weighing 60 kg (23). Thus, 500 mg/60 kg was selected as the final dose. This dose of IOE satisfied all standards for hazardous substances in the preclinical toxicity test (22). IOE and placebo were supplied by ShinWoo Co., Ltd., Anyang-si, South Korea.

Participants are randomly assigned to the IOE group or placebo group. The IOE group (*n* = 40) will be administered 500 mg IOE supplement/day orally, that is, one 250 mg capsule 30 min after breakfast and after dinner, for 12 weeks. The placebo group (*n* = 40) will be administered identically the same quantity of the placebo. The placebo was identical in appearance to the IOE capsule but was filled with crystalline cellulose. The participants will be requested to log supplement intake in a diary whenever they take it, which was turned in along with the bottle to the researcher at every visit. Compliance will be assessed by counting the remaining capsules at every visit, as in our previous study (13).

### Measurements of outcomes and safety

As this is one of a series of studies verifying the benefits of foods for muscle, selecting and measuring optimal outcomes and safety were based on our previous studies (13, 23).

### Outcomes

All outcomes were measured at baseline and after 12 weeks. The primary outcome measure was the change from the baseline in the peak torque (TQ) at 60°/s of knee extension/flexion representing muscle function at 12 weeks of IOE or placebo use. The secondary outcome measures were changes in appendicular skeletal mass (ASM)/height^2^ (kg/m^2^) (appendicular skeletal mass index, ASMI), ASM/weight x 100 (skeletal muscle mass index, SMI), total body fat (%), trunk body fat (%), hand grip (kg), serum creatinine, pyruvate, lactate, and high sensitivity C-reactive protein during the 12-week treatment period.

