## Data analyses

### Sample size determination

MedCalc version 20.113 (MedCalc Software Ltd, Ostend, Belgium) was used to calculate the sample size, based on our previous study (13). The sample size was adjusted to 40 participants per group to allow for 20% dropouts. The detailed estimation is described in our previous study (13).

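### hs-CRP is planned as a change score with baseline adjustment only if the groups differ: valid, but inefficient for a skewed marker, and the rank branch names no effect estimate

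*Protocol article*

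**What the plan says.** The Outcomes section of the protocol article defines the secondary outcomes as changes over the 12 weeks. The list ends with "high sensitivity C-reactive protein during the 12-week treatment period".

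Statistical analyses then gives one scheme:
- A Shapiro–Wilk "test will be used for the normality distribution assessment of all variables".
- For the test itself: "ANCOVA or rank ANCOVA will be used for the primary analysis".
- Covariates are not fixed in advance. The article plans "adjustments for the variables if there is a difference between the two groups at the start of the study"; exercise and diet are treated likewise where the groups diverge on them during the study.
- Quantities "all of which will be calculated as a delta".
- Intention-to-treat as the primary comparison of outcomes, with five imputed data sets for missing 12-week values of all variables.

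No log transformation, ratio measure or estimate to accompany the rank analysis is named. The switch from ANCOVA to rank ANCOVA when normality fails is implied, not written.

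On numbers, Sample size determination says "The sample size was adjusted to 40 participants per group to allow for 20% dropouts". No SD, correlation, effect or power for hs-CRP appears anywhere.

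**The concern.** One rule is applied to outcomes of different kinds. Torque, grip strength and ASMI can reasonably be compared as differences. hs-CRP is a concentration that is typically right-skewed, and effects on it are usually thought of in percent.

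On the raw scale the size of a change follows the starting level. A halving from 4 gives a delta of −2, and a halving from 0.4 gives −0.2, although the proportional change is the same. Ranking the deltas keeps that ordering. Including baseline removes part of the dependence, but the article makes baseline adjustment conditional on an observed group difference. After randomization a baseline test at the 5% level finds one in about 5% of trials, so baseline would usually stay out.

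Two things are at stake for this outcome: power from data already collected, and a result that says by how much the extract changes hs-CRP. hs-CRP is the only inflammation marker among the named secondary outcomes; TNF-α and IL-6 are listed in Table 3 as additional chemistry under the covariables.

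**Working it through.** **Inputs from the article.** 40 per group with 20% dropout gives 40 × (1 − 0.20) = 32 evaluable per group. The significance level is "0.05 will be considered statistically significant", taken as two-sided. The 32 cannot itself be re-derived, because the effect, SD and power behind it are left to an earlier publication.

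**Assumed inputs, none in the article.** hs-CRP is log-normal with log-SD 0.8–1.2 and baseline-to-week-12 log correlation ρ of 0.5–0.7, and treatment acts multiplicatively. The geometric mean ratio (GMR) is 0.6 (a 40% reduction) unless stated. A group difference at baseline is read as p < 0.05.

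**Step 1: log-scale ANCOVA by formula.** SE = SD × √(1 − ρ²) × √(2/n). With SD 1.0, ρ 0.6 and n = 32, SE = 1.0 × 0.8 × 0.25 = 0.20. The effect is −ln 0.6 = 0.511, so z = 0.511/0.20 = 2.55 and power ≈ Φ(2.55 − 1.96) = Φ(0.59) ≈ 72%. Simulation gives 71%.

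**Step 2: which branch would be used.** Shapiro–Wilk rejects the raw delta in 92–100% of simulated trials of this size, so the rank branch is the likely route. The other branch does no better: at log-SD 1.0, ANCOVA of the raw delta with baseline has 42–53% power, against 50–66% for rank ANCOVA of the delta with baseline and 64–79% for log-scale ANCOVA.

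**Step 3: where the power goes** (32 per arm, log-SD 1.0, ρ 0.6, GMR 0.6, 2,500 simulated trials).

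| Analysis | Power | Step loss |
|---|---|---|
| Log week-12 on arm and log baseline | 70.6% | – |
| Rank ANCOVA of week-12 value, baseline in | 67.8% | 2.8 |
| Rank ANCOVA of raw delta, baseline in | 58.0% | 9.8 |
| Rank analysis of raw delta, baseline in only if groups differ | 45.9% | 12.1 |
| Rank test of raw delta, no baseline | 45.4% | 0.5 |

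Ranking costs about 3 points, the raw-difference scale about 10, and the conditional use of baseline about 12. The conditional rule behaves almost like no adjustment.

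**Step 4: range over the assumptions** (32 per arm, GMR 0.6). Power is 48–94% for log-scale ANCOVA, 38–87% for rank ANCOVA of the delta with baseline, and 28–75% under the conditional rule. Compared within each scenario, the log-scale gain is about 7–15 points over rank ANCOVA with baseline and about 19–28 points over the conditional rule.

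**Step 5: smaller effects** (log-SD 1.0, ρ 0.6; log-scale ANCOVA v rank ANCOVA of delta with baseline v conditional rule).
- 32 per arm, GMR 0.8: 19.6% v 16.4% v 13.0%.
- 32 per arm, GMR 0.9: 7.7% v 7.7% v 7.5%.
- 40 per arm, GMR 0.8: 22.4% v 18.1% v 14.9%.
- 40 per arm, GMR 0.9: 9.0% v 8.1% v 6.6%.

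The gain over rank ANCOVA with baseline is at most about 4 points here, and every method has little power.

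**Step 6: validity.** With no treatment effect, rejection rates are 4.8% for log-scale ANCOVA, 5.1% for rank ANCOVA of the delta with baseline and 4.9% for the unadjusted rank test.

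**The case against.** The strongest reply is that this is a condensed journal article. The scale of one secondary biomarker, and the estimate reported beside a rank test, may be settled in an analysis plan that is not shown. The plan already provides for non-normality, its type I error is sound, and hs-CRP is one of nine secondary variables with no power claimed. This limits the point to a minor one. It does not remove it, because the article does state a method for its outcomes, and the point is that another method suits this outcome better.

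The wording also leaves room. The article says changes and delta, never absolute change. The delta clause directly follows the mention of exercise and diet, and the ANCOVA sentence speaks of the primary analysis. A plain difference applied to all outcomes is the natural reading, but it is a reading.

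The simulations generate exactly the data that a log-scale model assumes. Under illustrative departures the advantage shrinks. With transient spikes in 10% of values, power was 44% for log-scale ANCOVA, 36% for rank ANCOVA of the delta and 47% for rank ANCOVA of the week-12 value. With spikes and a floor at half the median, it was 34%, 32% and 42%. Log-scale ANCOVA still did better than the rank analysis of the delta, but it was not the best method. That part of the objection stands and shapes the sensitivity analysis proposed below.

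A reader might infer three stronger things. The first is that the planned test is invalid; the null simulations show otherwise. The second is that using ranks is the fault; ranks account for about 3 of roughly 25 points in the worked case. The third is that a fixed number of power points is lost; no hs-CRP figure in the article supports one, and the loss almost disappears for small effects. Nor does the article say that only a p-value will be reported. It simply names no estimate.

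**Conclusion.** The point holds as a minor matter of efficiency and reporting for one secondary outcome. The article's scheme, read naturally, analyses hs-CRP as a raw difference with baseline usually omitted. For a right-skewed marker that gives a valid but weaker comparison, and the rank branch names no effect in concentration or ratio units.

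The size is conditional. The larger gains in Step 4 need a true reduction near 40% and a roughly log-normal marker, and no eligibility criterion requires raised CRP. The ordering of log-scale ANCOVA over rank analysis of the delta survived the departures tried, though by as little as 2 points. The lack of a stated effect measure does not depend on any of these assumptions. The primary conclusion on knee torque is untouched.

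**What to change.** For hs-CRP, pre-specify:
- ANCOVA of the log week-12 value on arm and log baseline, with baseline included whether or not the groups differ at the start.
- Multiple imputation of hs-CRP on the log scale. The article does not state the imputation model. If it were a normal linear model on the raw scale (an assumption), 13–25% of imputed values were negative in simulation.
- The geometric mean ratio with 95% CI as the reported effect.
- Rank ANCOVA of the week-12 value on baseline as the sensitivity analysis, in case of spikes or values at the assay floor.

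Any other marker judged log-normal should be named in advance and treated the same way. The change is to wording only, needs no new data, and should be made before unblinding. The cost is that the result is a ratio rather than a difference in concentration units.
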